# Nurse-led self-management support after organ transplantation—protocol of a multicentre, stepped-wedge randomized controlled trial

**DOI:** 10.1186/s13063-021-05896-0

**Published:** 2022-01-06

**Keywords:** Nurse practitioners, Holistic nursing, Self-management, Patient participation, Behaviour mechanisms, Motivation, Goal, Self-efficacy, Self-control, Psychotherapy

## Abstract

**Background:**

Recipients of an organ transplantation face a number of challenges and often need to change their health behaviour. Good self-management skills are essential for optimal clinical outcomes. However, few interventions are available to support post-transplant self-management. To fill this gap, we developed a self-management support intervention offered by nurse practitioners. The primary aim of the study is to implement and test the effectiveness of the ZENN intervention in promoting self-management skills among heart, kidney liver and lung transplant recipients in comparison to standard care. The secondary aim is to assess the self-management support skills of nurse practitioners who will deliver the intervention.

**Methods:**

This multi-centre stepped-wedge randomized controlled trial will take place from September 2020 until May 2023. All departments will commence with inclusion of patients in the control period. Each department will be randomly assigned to a start date (step in the wedge) to commence the experimental period. Patients in the control period will receive standard care and will be asked to complete questionnaires at baseline (T0), 6 months (T1) and 12 months (T2), to assess self-management, self-regulation, quality of life and adherence. During the experimental period, patients will receive standard care plus the ZENN intervention and receive the same set of questionnaires as participants in the control period. Nurse practitioners will complete a baseline and follow-up questionnaire to assess differences in self-management support skills. Video recordings of outpatient clinic consultations during the control and experimental periods will determine the differences in nurses’ needs-thwarting and needs-supporting skills between the control and experimental period.

**Discussion:**

The ZENN intervention could be a useful approach to support patients’ self-management skills after organ transplantation and thus promote clinical outcomes as well as avoid adverse events.

**Trial registration:**

Dutch Trial Register NL8469. Registered on March 19, 2020.

**Supplementary Information:**

The online version contains supplementary material available at 10.1186/s13063-021-05896-0.

## Introduction

An organ transplantation is the preferred treatment for people with end-stage organ failure. However, after transplantation patients face several physical, social and emotional challenges. Patients need to deal with, for example, strict medication regimes, lifestyle changes and clinical appointments, social adjustment, and relationship instability [1–9]. They also have to cope with psychological consequences of transplantation such as acceptance of the organ, feelings towards the donor and changes in roles and relationships [10, 11]. Self-management can be defined as “the individual’s ability to manage the symptoms, treatment, physical and psychosocial consequences and lifestyle changes inherent with a chronic condition” [12]. In this definition, it is implied that self-management needs to be holistic in approach, whereby self-management of both medical and psychosocial aspects is required. Despite the scarcity of organs and the importance of effective self-management for patient outcomes, adherence to behavioural recommendations and therapeutic regimens after transplantation is substantial [4, 13, 14]. Optimizing patients’ self-management skills has received increasing attention, as this is essential for patient outcomes and can help reduce non-adherence [4, 13, 14], decrease healthcare costs [15] and improve patients’ quality of life [16].

Currently, there are few interventions to promote self-management among transplantation patients and these tend to focus mainly on medication adherence [17–19]. Moreover, these interventions have not been able to demonstrate effectiveness [18]. Patients after organ transplantation have specific needs in receiving self-management support, but the current healthcare system does not meet these needs [20–24]. Patients wish to discuss medical, social and emotional issues, receive information about their disease and receive tailored instructions [20].

Patient empowerment is also a crucial component of effective self-management. This concept can be defined as “a social process of recognizing, promoting and enhancing people’s abilities to meet their own needs, solve their own problems and mobilize the necessary resources in order to feel in control of their own lives” [25]. Patients indicate the need for support in becoming more self-confident and taking control over their post-transplant life, for example through positive feedback and care personalized to individual needs [21]. Linked to patient empowerment is the desire for shared-decision making. The extent to which patients want to participate in the decision-making varies [23], but there is a need for greater partnership between the patient and the professional. This partnership is a prerequisite for supporting self-management skills [21].

In clinical practice, physicians in outpatient clinics have limited time to address self-management issues and often lack the training in self-management support and empowerment skills to do so. Nurse practitioners (NPs) are more suitable to support patients in developing self-management skills and self-management support is an important part of the job description of nurses [26–28]. Still, nurses and NPs indicate the need for training to develop the necessary skills to support patients’ self-management [29, 30].

In response to the need for a more holistic, tailored and patient-centred approach to self-management support among patients and communication skills training among nurses, we initiated a project to develop a self-management support intervention. Based on previous studies of our team [20, 22, 23], we developed a self-management (support) intervention which is called the ZElfmanagement Na Niertransplantatie (ZENN; Dutch acronym for self-management after kidney transplantation) intervention [22]. This intervention included four key elements: (1) a general structure with room for individual tailoring, (2) a holistic approach, (3) shared-decision making between NP and patient, and (4) patient empowerment. The overall goal of the intervention is to enhance patients’ self-management skills in order to integrate their treatment- and life goals and subsequently optimize their quality of life and health-related outcomes.

In an initial qualitative pilot study among 26 kidney transplant recipients, we assessed the acceptability and feasibility of this intervention. Patients valued the ZENN intervention and felt that this should be offered to all patients who have received a kidney transplant, particularly in the first year post-transplant [31]. Moreover, professionals reported the added value of the holistic approach in building a relationship of trust and promoting well-being [31]. We concluded that it was worthwhile to test the effectiveness of the ZENN intervention in future research.

In this article (version 1; January 2021), we describe the design of the ‘aanZET’-study. In this study, we will test the effectiveness of the ZENN intervention in promoting self-management skills among heart, liver, lung and kidney transplant recipients in comparison to standard care. The aims of the study are (1) to assess if the intervention has an effect on patients’ self-regulation and self-management skills, quality of life, medication adherence, coping and self-efficacy, controlling for socio-demographic and medical characteristics; (2) to assess if these changes are sustained over time after completion of the intervention; and (3) to test if the training and delivering the intervention has an effect on self-management support skills among NPs who provide outpatient care after transplantation.

## Methods/design

### Study design and randomization

This multi-centre study in the Netherlands has an unblinded stepped wedge cluster randomized design [32] with pre- (T0) and post-intervention measures after six months (T1), with a follow up after twelve months (T2). The framework of this trial is superiority, whereby we will compare the outcomes between the control and intervention group, and between baseline and follow up data. Seven departments of five University Medical Centres will participate in the study, four kidney transplantation units, one heart transplantation unit, one liver transplantation unit and one lung transplantation unit. The coordinating centre is Erasmus MC, department Nephrology and Transplantation. This department is responsible for coordinating the study, distributing the questionnaires, training of the NPs and the data analysis. A steering committee is present to contribute ideas and to oversee the process.

Given the nature of the programme and the fact that NPs are trained in delivery of the intervention and communication skills, the NPs delivering the intervention cannot be blinded to the group allocation. Therefore, randomization will be performed at the department level. This will be carried out by an independent professional not involved in the study using sealed opaque envelopes. The envelopes with department names and envelopes with start date will be prepared and shuffled by the researcher. The independent professional then randomly chooses the envelopes. All seven participating departments commence the study with standard care i.e. the control period (see Fig. 1) in September 2020. The timing of transition of departments from control to experimental  period is randomized. The first department will be randomized to commence the experimental period in March 2021. During the experimental period, patients receive standard care plus the ZENN intervention. Patients in the control period are different from the experimental period patients, meaning that they will not cross-over.

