**Fig. 1 Fig1:**
[figure not shown]
Flowchart of the study

In the month prior to the initiation of the experimental period for each department, the NPs will be trained in the delivery of the intervention. At this point in time, there will still be patients in the control period who are yet to complete the follow-up measure. During this month they may receive care in the form of a standard consultation from this NP. Therefore, there is potential for ‘contamination’ of these control period patients in the sense that their NPs will have already received the training associated with the intervention. To limit the risk of contamination, the following strategies will be put in place: standard care protocol will be used in all consultations for control period patients, and the questionnaires will not be administered by the NP but will be sent out by the researcher.

The ZENN intervention will be conducted in the outpatient clinic of each participating department. Due to the COVID-19 pandemic, the possibility of carrying out the intervention through tele-medicine is being examined. For the schematic overview of the inclusion, see Fig. 1. To enhance the validity of the study, the Standard Protocol Items: Recommendations for Interventional Trials (SPIRIT) guidelines [33] will be followed.

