### Eligibility criteria

#### Patients

Eligible patients are heart, kidney, liver or lung transplant recipients who have received a transplant in one of the participating centres. The NP will ask patients to participate and hand out the written information on the study. Inclusion criteria are: over 18 years old, between two and thirteen months elapsed after transplantation, sufficient command of the Dutch language and the presence of a functioning graft. Exclusion criteria are cognitive limitations, participating in other lifestyle or self-management promoting programmes which could influence the outcome, and in case of kidney transplant recipients, an expected need for renal replacement therapy within 3 months of inclusion.

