### Training

At the moment of transition to the experimental period, NPs will receive training in communication skills and intervention background by a psychologist ([name]). Both trainers were part of the team who developed the ZENN intervention. The content of the standardized training includes knowledge of the steps in the programme protocol, theoretical knowledge of behaviours change techniques, and practicing these techniques through role-play. NPs learn to activate patients to generate their own solutions rather than focusing on the problems and achieve progression towards personal goals in short space of time. The training consists of two blocks of three hours given on the same day. Due to the COVID-19 pandemic, the possibility of carrying out the training through e-learning and video conferencing is being examined. In addition, there is a booster session once implementation has begun with the aim of discussing cases and optimizing standardization between NPs. The experimental period starts immediately the day after the one-day training has been completed. An extensive description of the training according to the CRe-DEPTH criteria developed by Van Hecke et al. (2020) [38] can be found in Supplement A.

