### Sample size

The sample size calculation is based on a power calculation for the primary outcome i.e. the Skills and Technique acquisition scale of the heiQ at T1. Previous studies have shown effect sizes (Cohen’s *d*) of similar interventions on the Skills and Technique Acquisition scale of 0.17, 0.50, 0.25, 0.50, 0.31 and 0.59 [49–54]. Based on these previous results, we estimate the effect size of the intervention to be 0.38, which is the average effect size observed in the previous studies. Using an ANCOVA model applied at the patient level, with an adjustment for baseline Skills and Technique Acquisition and treatment group (pre- or post-intervention), 82 patients per group are needed to obtain a power of 80% to detect a significant effect of the intervention, at a two-sided significance level of .05. To account for the effects of adjustment for covariates, dropout and missing data, and contamination, we aim to include 100 patients per group, 200 in total. Note that the ANCOVA model assumed in the power analysis differ slightly from the linear mixed model described for the primary analysis below.

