### Strengths and limitations

Some strengths and weaknesses of the study design can be identified. The overall strength of the study is that we give patients in the experimental group the opportunity to participate in an intervention that may meet the needs of patients for holistic and tailored self-management support. Existing interventions have an insufficient tailoring to individual needs [18, 22, 56]; therefore, this intervention has the potential to make an important contribution to the lives of transplant recipients and approaches available to post-transplant professionals.

A strength of the stepped wedge design in this study is that the participating departments will be randomized so that, every department will have the opportunity to participate in the experimental period. With a classical randomization, whereby patients, NPs, or departments would be randomized into the control and the experimental arm, half of the patients would not receive the intervention or half of the NPs would not be trained. Randomization at the patient level is not possible due to the fact that nurses learn communication techniques and it is not possible to switch between these techniques during the control and experimental arm. Moreover, randomization at the NP level would be less preferable. Some departments have only one NP and if they will be randomized into the control arm, a whole department would not be able to participate in the intervention.

A limitation of the stepped wedge design is the risk of contamination of control period patients. Although the stepped wedge design eliminates to a great extent control-period patients being treated by a nurse trained in the intervention, there will be some patients at the end of the control period who are treated by and who undergo follow-up measurement once their NP has been trained. This means that it is possible that the patients at the end of the control period may be ‘contaminated’. We will register which control period patients fall into this ‘contamination phase’. We expect that this will be a small group and not be of influence on the findings.

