## Trial status

Start of inclusion; September 2020, expected end of inclusion May 2022.

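### T0 in the experimental period may already include routine consultations with a ZENN-trained NP, but contamination is registered and tested only for control-period patients

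*Protocol article*

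**What the plan says.** **Status of T0.** Study design and randomization describes a design "with pre- (T0) and post-intervention measures after six months (T1"), with a further follow-up at twelve months (T2).

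**Entry and timing.** Patients are eligible with "between two and thirteen months elapsed after transplantation" and are invited by the NP (Eligibility criteria, Patients). "The first department will be randomized to commence the experimental period in March 2021" (Study design and randomization). Trial status gives "Start of inclusion; September 2020, expected end of inclusion May 2022".

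**When NPs are trained.** The text after Fig. 1 says: "In the month prior to the initiation of the experimental period for each department, the NPs will be trained in the delivery of the intervention". It adds that control patients may have standard consultations with the trained NP during that month. The Training section says: "The experimental period starts immediately the day after the one-day training has been completed".

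**Contamination.** The text after Fig. 1, the Data analysis section, and Strengths and limitations treat contact between a control-period patient and a trained NP as possible contamination. Such patients are registered and compared with other controls at T1 and T2, and the main multivariate analysis is adjusted if they differ significantly. Strengths and limitations also says that "nurses learn communication techniques and it is not possible to switch between these techniques". No corresponding step is described for experimental-period patients before T0.

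**Where T0 is used.** It enters the ANCOVA behind the sample size ("with an adjustment for baseline Skills and Technique Acquisition and treatment group"), the linear mixed model (T0, T1 and T2), the within-period T0-T1 and T0-T2 comparisons, and the check that the groups are comparable. The T1 test that Data analysis labels primary does not use T0. The Sample size section, however, refers to a linear mixed model as the primary analysis.

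**The concern.** After a department switches, every patient it recruits is invited by an NP trained at or before the switch. A patient included some months later, and some months after transplantation, may already have seen that NP in routine care. By the protocol's own reasoning this is exposure: the same standard consultation with a trained NP, given to a control patient, has to be registered and tested.

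If the contact raises the heiQ skills score, T0 in the experimental period already carries part of the effect. Conditioning on T0 or subtracting it then removes that part, and the bias is toward no effect. The T0 comparison of the two periods, meant to show comparability, could present the same shift as baseline imbalance.

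**Working it through.** **1. The planned sample size.** Inputs from Sample size: d = 0.38, 80% power, two-sided 0.05. Without T0, n = 2 × ((1.96 + 0.84)/0.38)² = 109 per group. With ANCOVA, n is multiplied by (1 − r²), where r is the T0-T1 correlation. The protocol does not give r. At r = 0.5 the result is 82, the stated figure (r = 0.4 gives 92, r = 0.6 gives 70). I use r = 0.5 as an assumption below.

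**2. Possible exposure before T0.** This is at most min(months since training, months since transplantation). Assume time since the switch is uniform on 0 to L months and time since transplantation is uniform on 2 to 13 months. Then

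- P(exposure > x) = 1 − x/L for x up to 2 (and below L);
- P(exposure > x) = (1 − x/L) × (13 − x)/11 for x from 2 to the smaller of L and 13.

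For L = 15 (start of March 2021 to end of May 2022), P(> 3 months) = (12/15) × (10/11) = 0.73.

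| L (months) | Mean exposure (months) | Share above 3 months |
|---|---|---|
| 2 | 1.0 | 0% |
| 7 | 3.2 | 52% |
| 10 | 4.2 | 64% |
| 15 | 5.3 | 73% |

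These are upper bounds, because they count NP outpatient care from the day of transplantation. If all patients entered at 2 months after transplantation, exposure could not exceed 2 months. If a department filled its places right after the switch, it would be near zero. The average target is 100/7, about 14 experimental patients per department, so quick filling is possible. The protocol gives neither the spread of inclusion after each switch nor the frequency of NP visits before inclusion.

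**3. Effect on the estimates.** Let f be the share of d already present at T0 in the experimental period, with the T1 difference equal to d and equal SDs. Then

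- T1 contrast without T0: d;
- ANCOVA: d(1 − r·f);
- difference in T0-T1 change: d(1 − f).

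The within-period change in the experimental period is short by f·d. Residual SDs are 1, √(1 − r²) and √(2(1 − r)) respectively. At r = 0.5, with power at patient level as in the protocol's own calculation:

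| f (assumed) | ANCOVA estimate | Power, 82 / 100 per group | Change estimate | Power, 82 per group |
|---|---|---|---|---|
| 0 | 0.380 | 80% / 87% | 0.380 | 68% |
| 0.10 | 0.361 | 76% / 84% | 0.342 | 59% |
| 0.25 | 0.333 | 69% / 78% | 0.285 | 45% |
| 0.50 | 0.285 | 56% / 64% | 0.190 | 23% |

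The T1 contrast without T0 stays at 0.380 for every f, with power 68% at 82 and 77% at 100 per group. ANCOVA keeps the higher power until 1 − r·f = √(1 − r²), that is f = (1 − 0.866)/0.5 = 0.27. Below that value the cost of adjustment is bias in the estimate rather than loss of power.

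**4. The mixed model.** A plain contrast between periods at T1 or T2 is unaffected. Bias arises only if T0 is a covariate, if the period means at T0 are constrained to be equal, or if the effect is read as a difference in change. The text does not settle which of these applies.

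**The case against.** The strongest reply is that T0 does precede the intervention under test. ZENN is a series of structured sessions, and nothing says that any is given before T0. Earlier contact is routine care from a nurse with new communication skills, so f may be small. The remark about not switching techniques explains why patients within a clinic cannot be randomised to concurrent arms. It does not say that a routine consultation raises heiQ scores. The protocol also expects contamination of controls to be minor. This stands as far as size goes. It does not remove the asymmetry, because contaminated controls likewise receive only standard consultations, and the protocol still registers and tests them.

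A second reply is that the main contrast is safe. That is right for the T1 test labelled primary and for any plain T1 or T2 contrast between periods. It does not cover the within-period changes, or a mixed model that uses T0 in one of the ways listed above.

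A reader might go further and infer that many experimental patients will have months of trained-NP care before T0, or that the effect will shrink by a stated percentage. The documents support neither. The exposure figures rest on assumed inclusion timing and are upper bounds, and no source gives a value for f.

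Visit logs and sensitivity analyses are also details that a condensed article may leave to a fuller document. The point here is narrower: the article states a contamination rule for one period only and labels T0 as pre-intervention.

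**Conclusion.** The point holds in a limited form. T0 in the experimental period need not be free of trained-NP contact, and the contamination provisions do not cover this. If such contact raises scores, T0-adjusted and change-based estimates are biased toward no effect, by r·f and f of the effect respectively. At r = 0.5 and f between 0.10 and 0.50, that is 5% to 25% for ANCOVA and 10% to 50% for change. Both r and f are assumptions. Mean possible exposure runs from near zero to about 5 months, depending on how inclusion is spread after each switch. The T1 comparison between periods without T0 is not affected.

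**What to change.** - Extend the contamination registration to experimental-period patients: number and dates of consultations with a trained NP before T0, or at least time since training at T0.
- Report the mixed-model T1 and T2 contrasts between periods without conditioning on T0, beside any T0-adjusted or change-based estimate.
- As a sensitivity analysis, examine T0 scores by pre-T0 exposure, so that a shift in the comparability check can be interpreted.
- Describe T0 as measured at inclusion rather than as pre-intervention.
- Reconcile the text after Fig. 1 with the Training section on when training takes place, since this sets when exposure starts. The two agree only if training falls on the last day before the switch, yet the former allows for control consultations with a trained NP during that month.

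**Cost.** One extra variable, best captured prospectively, and lower precision in the contrast that does not use T0: at r = 0.5, f = 0 and 100 per group, power is 77% against 87% for ANCOVA. It should therefore stand beside the adjusted estimate and not replace it. An analysis restricted to unexposed patients should be exploratory only, because it selects on calendar time and on time since transplantation.
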